### 2.12. Data Analysis

The primary outcome is the live birth rate. Secondary outcomes include (1) ovulation rate; (2) ongoing pregnancy rate at gestation 8–10 weeks; (3) multiple pregnancy rate; (4) miscarriage rate: loss of an intrauterine pregnancy before 20 completed weeks of gestation; (5) change in hormonal profile: FSH, LH, T, SHBG, and DHEAS; (6) change in metabolic profile: glucose and insulin concentrations, cholesterol, triglycerides, HDL-C, and LDL-C; (7) side effect profile; (8) change in QOL; (9) change in symptoms of anxiety and depression; and (10) credibility assessments.

The analysis will use an intent-to-treat (ITT) approach to examining differences in the live birth rates among the four treatment arms. Primary efficacy analysis will be done by comparing the treatment groups with respect to the primary outcome of live birth using the Pearson Chi-square test. For the secondary, supportive analysis, we will fit a logistic regression model to compare the treatment arms with respect to the primary outcome of live birth, adjusting for other factors such as randomization stratification of study site and prior exposure to study medications. The analysis of other secondary outcomes measured over time will entail the application of statistical methods that have been developed for correlated data since repeated observations will be made over time on each individual. For secondary outcomes such as hormone levels, a linear mixed-effects model will be fit where the main independent variables will be treatment group, time, and their interaction as well as the designed randomization stratification factors as covariates. Logistic regression models will be used in secondary analyses to evaluate the predictive value of treatment arm, clinical site, prior exposure to CC, body mass index, and other explanatory variables on binary outcomes (e.g., singleton live birth, abortion). Cox proportional hazards models and a Kaplan-Meier method will be applied to compare time to pregnancy in the treatment groups. 

Adverse events will be categorized and percentage of patients experiencing adverse events and serious adverse events in this trial will be documented. Chi-square tests will be performed to examine differences in the proportion of total and categories of adverse events within each treatment arm. For each Data and Safety Monitoring Board (DSMB) report, a list and summary of the reported adverse events will be presented in a blinded fashion, unless otherwise formally requested. Unblinding of treatments will take place after all participants have delivered or reported final outcomes to the DCC or when there are medical emergencies.

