In PCOS women with ovulatory dysfunction, several nonrandomized trials revealed that repeated acupuncture treatments decreased total testosterone and other sex steroid levels, reduced LH/follicle-stimulating hormone (FSH) ratio, and improved menstrual frequency without negative side effects [17–19]. In a randomized controlled trial (RCT), fourteen acupuncture treatments, with combined electrical and manual stimulation of the needles during 16 weeks and 16 weeks of physical exercise compared with no intervention, improved menstrual bleeding pattern and decreased high levels of sex steroid precursors, estrogens, androgens, and glucuronidate androgen metabolites in women with PCOS [20]. Acupuncture was superior to physical exercise when compared directly after the treatment period. In a quasi-randomized study, daily abdominal acupuncture during 6 months improved menstrual frequency and decreased circulating testosterone more effectively than metformin during 6 months [21]. Recently in another RCT, 12 treatments of true acupuncture were compared with control acupuncture using placebo needles during 8 weeks and similar ovulation rates were found in both groups of women with PCOS [22]. 

Findings from previous clinical and experimental studies indicate that acupuncture may induce ovulation and improve pregnancy in women with PCOS. However, the methodological quality of these studies is of varying quality, and none were designed to investigate pregnancy or more importantly live birth. We sought to address these gaps in knowledge by designing an RCT to examine the effects of acupuncture on live birth in women with PCOS. The objective of the present trial is to test the following three hypotheses in anovulatory women with PCOS: (1) true acupuncture and CC are more likely to result in live birth than control acupuncture and CC, (2) control acupuncture and CC are more likely to result in live birth than true acupuncture and placebo CC, and (3) true acupuncture and placebo are more likely to result in live birth than control acupuncture and placebo CC.

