
### 2.2. Study Design

This is a multicenter, randomized, double-blinded, controlled, 2 by 2 factorial clinical trial for PCOS women in China, with study treatment during 4-month cycles. Participants are randomized to receive either an initial oral dose of 50 mg of CC or placebo CC from day 3 to day 7 of the cycle [4] in combination with one of the two acupuncture procedures. The starting date for CC is not expected to affect the treatment outcome [28]. In order to maintain the double-blinding for the medication, CC and placebo CC were packaged in identically appearing numbered study kits which were then directly shipped to each clinical site. For acupuncture, all patients will receive either true or control acupuncture treatment. 

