### 2.11. Sample Size Calculations

The overall live birth rate for women to receive CC is estimated to be 20% during the 4-month period according to Chinese Obstetrics and Gynecology (Second Edition). Due to lack of existing data on the effectiveness of acupuncture, we cannot rely on the literature for samples size determination. Instead we hypothesize that the order of effectiveness of the treatments is as follows: True acupuncture and CC > Control acupuncture and CC,  control acupuncture and CC > True acupuncture and placebo CC,  true acupuncture and placebo CC > Control acupuncture and placebo CC. The respective live birth rates are projected with 10% difference as follows and the average rate among four arms is 15% (Table 3).

 Using a two-sided trend test and with an effective sample of 200 per group, our study is designed to have >80% power at the significance level of 0.015 (we have three primary hypotheses). The sample size has been inflated from 200 to 250/arm to allow for a dropout rate of 20%, totally 1000 cases for four arms. 

There have been multiple trials to study the effects of CC in PCOS women. The primary aim of this trial is not to reassess the efficacy of CC. The aim is to elucidate the additional efficacy of acupuncture in combination with CC, or acupuncture alone. Acupuncture is compared with CC because CC has been demonstrated to be superior to metformin [4]. The previous study design is used as a role model since it was the best executed and most cited trials in this area. [name] chairs the Steering Committee of this trial, and [name] leads the DCC for another trial using CC in PCOS women. They have considered all related studies, although the power calculation involved inevitably some assumptions. The significance level of 0.015 is approximately 0.05/3 because in this study the overall significance level is controlled to 0.05 after correcting for the multiple comparisons involving three primary hypotheses.

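### The primary chi-square test is not tied to an acupuncture contrast, and the stated power of more than 80% does not hold for true versus control acupuncture on top of CC

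*Protocol article*

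**What the plan says.** Arms: A is true acupuncture + CC, B control acupuncture + CC, C true acupuncture + placebo CC, D control acupuncture + placebo CC.

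- **Design (Section 2.2):** a "2 by 2 factorial clinical trial".
- **Aim (Section 2.11):** "The primary aim of this trial is not to reassess the efficacy of CC". The same paragraph gives the question as what acupuncture contributes, either added to CC or alone.
- **Hypotheses (Section 1):** three directional statements. A over B: "true acupuncture and CC are more likely to result in live birth than control acupuncture and CC". B over C: "control acupuncture and CC are more likely to result in live birth than true acupuncture and placebo CC". C over D: "true acupuncture and placebo are more likely to result in live birth than control acupuncture and placebo CC".
- **Sizing (Section 2.11, Table 3):** a two-sided trend test with 200 effective women per arm, more than 80% power at 0.015, with 0.015 explained as roughly 0.05/3 for three primary hypotheses. Projected live birth rates are A 25%, B 15%, C 15%, D 5%.
- **Primary analysis (Section 2.12):** an intent-to-treat approach to "examining differences in the live birth rates among the four treatment arms", carried out by "comparing the treatment groups with respect to the primary outcome of live birth using the Pearson Chi-square test". The degrees of freedom and the contrasts are not given. The supportive logistic model also compares treatment arms.

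**The concern.** The design, the aim, the sizing test and the primary test do not point at the same quantity. A chi-square across four arms responds to any difference among them, including one caused wholly by CC. So does a trend across arms ordered with the CC arms on top. Rejecting either does not show that acupuncture works.

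If the test is instead meant pairwise, it can answer the acupuncture questions. But the power statement was derived for another test, and it has to be checked whether it carries over. At stake are a positive primary result that says nothing about acupuncture, or a real benefit of adding acupuncture to CC that the trial has about an even chance of missing.

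**Working it through.** **Inputs.** Table 3 rates; 200 effective and 250 randomised per arm (Sections 2.3 and 2.11); two-sided alpha 0.015 (Section 2.11), z = 2.432.

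**1. The plan's own figures.** Dropout: 200/(1 − 0.20) = 250, as stated. Trend test (Cochran-Armitage, scores 3, 2, 1, 0, mean 1.5, 200 per arm):
- Signal: 200 × (1.5×0.25 + 0.5×0.15 − 0.5×0.15 − 1.5×0.05) = 60.
- Null SD: √(0.15×0.85×200×5) = 11.29. SD under Table 3: 10.89.
- (60 − 2.432×11.29)/10.89 = 2.99, so power is 99.9%.

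More than 80% is true as an inequality for the trend test; about 75 per arm would give 80%.

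**2. Global reading, with no acupuncture effect.** Averaging Table 3 over acupuncture gives CC (25+15)/2 = 20% and placebo CC (15+5)/2 = 10%. Assume rates 20/20/10/10. The 3-df noncentrality is n·Σ(p − p̄)²/[p̄(1 − p̄)]; the critical value at 0.015 is 10.47.
- 200 per arm: 200×0.01/0.1275 = 15.69, rejection 84% (85% by simulation).
- 250 per arm: 19.61, rejection 93%.
- CC effect of only 5 points (assumed 20/20/15/15), 200 per arm: 200×0.0025/0.144375 = 3.46, rejection about 17%.

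**3. Pairwise reading.** Power = Φ[(|p1 − p2| − z·√(2p̄(1 − p̄)/n)) / √((p1(1 − p1) + p2(1 − p2))/n)].
- A vs B, n = 200: (0.10 − 2.432×0.0400)/0.0397 = 0.068, so 53%. At n = 250: 64%. For 80%, 342 per arm are needed.
- C vs D, n = 200: (0.10 − 2.432×0.0300)/0.0296 = 0.914, so 82%. At n = 250: 91%.
- B vs C: Table 3 gives 15% for both, so this test rejects at about its alpha.

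**4. Pooled acupuncture comparison (A+C vs B+D).** Rates are (25+15)/2 = 20% and (15+5)/2 = 10%, with 400 women on each side: (0.10 − 2.432×0.02525)/0.0250 = 1.543, so 94%. A Mantel-Haenszel test stratified by CC gives 94.7% by simulation.

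**5. At least one acupuncture contrast significant.** A vs B and C vs D share no women, so under Table 3 the chance is 1 − (0.473×0.180) = 91% (92% by simulation).

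**6. If acupuncture works only without CC.** By simulation at 200 per arm with assumed rates 15/15/15/5 or 20/20/15/5, the pooled test at 0.05 has about 57% or 52% power. C vs D alone at 0.015 has about 84%.

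**7. Scale.** Table 3 has the same risk difference in both strata (10 and 10 points). Its odds ratios differ: (0.25/0.75)/(0.15/0.85) = 1.89 and (0.15/0.85)/(0.05/0.95) = 3.35.

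**The case against.** The case on the other side is substantial.

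- **The global reading is the less likely one.** Three arm-versus-arm hypotheses and an alpha near 0.05/3 make sense for pairwise tests; a single omnibus test would need no split. This stands. A reader might infer that the primary result will be significant from CC alone. The documents do not support that: it needs both the less likely reading and a CC effect near 10 points, and step 2 shows how quickly the risk falls with a smaller effect.
- **The pairwise reading wastes nothing overall.** A reader might infer that it throws away half the acupuncture data. That is true of each test alone, but A vs B and C vs D together use all four arms and match the stated aim. A factorial layout does not oblige anyone to analyse margins. This stands too: step 5 gives 91% for at least one success, close to the pooled 94%. What is lost is power for A vs B specifically, and a pooled estimate.
- **Pooling has its own cost.** Step 6 shows that it does worse if acupuncture works in only one CC stratum. This stands, and it rules out making the pooled test a gatekeeper.
- **A condensed article may leave contrasts to the analysis plan.** This stands as far as it goes, so the absence of a pooled analysis or interaction is not an error in itself. But the article does state a primary test and a power figure, and these do not fit each other or the aim.

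**Conclusion.** The point holds in limited form. The primary test as worded does not say which comparison carries the acupuncture claim. One permitted reading, the 3-df test, cannot answer the acupuncture question whatever the size of the CC effect. On the likelier pairwise reading, the stated power of more than 80% is met for C vs D (82%) but not for A vs B (53% at 200 per arm, 64% at 250), because that figure belongs to the trend test. Data already to be collected support a pooled acupuncture comparison with about 94% power at the same alpha.

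These figures rest on the Table 3 rates, two-sided 0.015 and 200 effective women per arm unless stated. The pooled figure also assumes a similar absolute benefit with and without CC, as Table 3 projects. Pooling does not raise the power of A vs B itself.

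**What to change.** - **Section 2.12:** state that the primary inference is not the 3-df test but the acupuncture contrasts A vs B and C vs D.
- **Add** a prespecified Mantel-Haenszel comparison of true versus control acupuncture (A+C vs B+D), stratified by CC or placebo CC. State its share of alpha, and do not make the two simple contrasts conditional on it. If all three hypotheses keep 0.015, they use 3 × 0.015 = 0.045 and leave 0.005. At 0.005 (z = 2.807) the pooled power is Φ[(0.10 − 2.807×0.02525)/0.0250] = Φ(1.165), about 88%. A different split is possible but must be written down.
- **Report** the pooled effect, both simple effects and the acupuncture by CC interaction as risk differences with 95% confidence intervals. On that scale the projected rates show no interaction.
- **Section 2.11:** restate power for the tests actually used, including the shortfall for A vs B.

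The cost is wording, with no extra women or visits, and it can be settled before unblinding, which Section 2.12 places after final outcomes are reported except in medical emergencies. A small downside is that the pooled estimate averages over CC and loses power if acupuncture works in only one stratum, so it must be shown beside the simple effects.

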## 1. Introduction

Polycystic ovary syndrome (PCOS) is the most common endocrine disorder in women of reproductive age. It is characterized by ovulatory dysfunction, hyperandrogenism, and polycystic ovaries (PCO) and affects 5–10% of premenopausal women [1]. In addition to irregular menses, hirsutism, and infertility, women with PCOS may display a number of metabolic abnormalities including hyperinsulinemia, insulin resistance, dyslipidemia, and obesity [2]. Clomiphene citrate (CC) is considered as the first line treatment to induce ovulation in women with PCOS. A compilation of published results from 5,268 patients revealed an ovulation rate of 73% per cycle per patient, pregnancy rate of 36% per patient, and live birth rate of 29% per patient during a six-month treatment [3]. Women who do not ovulate while receiving the maximum 150 mg dose are considered to be CC resistant and those who do not conceive after an ovulatory response are considered clomiphene failures. Both appear to be common [4], necessitating the search for adjuvant therapies to treat infertility in women with PCOS. 

Inability of CC to induce ovulation is more likely in patients who are obese, insulin resistant, and hyperandrogenic compared with those who do respond [5]. The mechanism of CC failures may partly be explained by a peripheral anti-estrogenic effect at the level of endometrium and cervical mucus or by hypersecretion of luteinizing hormone (LH). Side effects of CC are related to its combined estrogenic and antiestrogenic properties, which include hot flushes, breast discomfort, abdominal distension, nausea, vomiting, nervousness, sleeplessness, headache, mood swings, dizziness, hair loss, and disturbed vision [4]. Approximately 7% of pregnancies resulting from CC-induced ovulation are twin pregnancies and 0.5% are triplet pregnancies [6]. 

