### 2.5. Study Specific Visits and Procedures

Each specific visit and measurement is summarized in Table 2. Baseline measures include fasting FSH, LH, total testosterone (T), estradiol (E2), sex hormone binding Globulin (SHBG), dehydroepiandrosterone sulfate (DHEAS), glucose and insulin concentrations, cholesterol, triglycerides, high-density lipoprotein cholesterol (HDL-C), low-density lipoprotein cholesterol (LDL-C) and height, weight, hip, waist measurements, and vital signs. Neither cervical mucus nor endometrial lining will be monitored in this large clinical trial as these are not routinely monitored in clinical practice. Also questionnaires for assessments of health related quality of life (QOL) are filled in: the short form 36 (SF 36) [33], the Polycystic Ovary Syndrome Questionnaire (PCOS-QOL) [34], and the Chinese Quality of life (ChQOL) [35]. Questionnaires for symptoms of anxiety and depression are Zung Self-Rating Anxiety Scale (SAS) [36] and Zung Self-reported Depression Scale (SDS) [37]. All questionnaires used in this trial are validated scales. 

The TCM diagnosis will be made by an experienced TCM doctor in each participating site according to a standard questionnaire. Syndrome differentiation in TCM is the comprehensive analysis of clinical information gained by the four main diagnostic TCM procedures: observation, listening, questioning, and pulse analysis [38]. In PCOS, patients are empirically differentiated to be four categories: (1) phlegm-dampness syndrome, (2) blood stasis syndrome, (3) phlegm and blood stasis, and (4) liver stagnation [39]. The TCM diagnosis will not affect the treatment protocol, and it will enable us to explore its effect on the treatment success in a secondary analysis.

All baseline measures will be repeated in all subjects at the end of visits. Blood samples (including the safety labs) will be collected and shipped to the core lab. Credibility check questionnaires are completed on the third acupuncture treatment and the last acupuncture treatment [40–42].

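### The live-birth comparison uses none of the prognostic baseline values the trial already holds; a small prespecified covariate set would add a little power at low cost

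*Protocol article*

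**What the plan says.** The protocol article, section 2.12, compares the arms "with respect to the primary outcome of live birth using the Pearson Chi-square test". No covariate enters that test.

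A logistic model follows as a secondary, supportive analysis of the same outcome, "adjusting for other factors such as randomization stratification of study site and prior exposure to study medications". Site and prior exposure are given there as examples, so the list is open.

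Later in the same section, secondary logistic models are to "evaluate the predictive value of treatment arm, clinical site, prior exposure to CC, body mass index, and other explanatory variables on binary outcomes", with singleton live birth among the examples. This is the only place in the analysis section where BMI is named.

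The Introduction says: "Inability of CC to induce ovulation is more likely in patients who are obese, insulin resistant, and hyperandrogenic". Section 2.5 lists height, weight, total testosterone, SHBG, DHEAS and "glucose and insulin concentrations, cholesterol, triglycerides" among the baseline measures. Age is an eligibility item (20 to 40 years, section 2.1).

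**The concern.** The authors name obesity, insulin resistance and hyperandrogenism as marks of women who fail to ovulate on clomiphene. They measure all three before treatment and treat BMI as explanatory for a live-birth outcome elsewhere in the plan. Yet the main comparison of arms on live birth uses none of them, and the supportive comparison does not name them.

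In a randomised trial, prespecified adjustment for prognostic baseline values gives a somewhat more powerful test and deals with chance imbalance. A versus B asks whether acupuncture adds to clomiphene, which section 2.11 gives as an aim, and among the contrasts with a projected difference it has the least power. An open covariate list also leaves room to choose covariates after the data are seen.

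**Working it through.** **Inputs.** Table 3 rates: A 25%, B 15%, C 15%, D 5%. Section 2.11: two-sided test, level 0.015 (z = 2.432), 200 effective per arm, 20% dropout, power above 80%. Section 3.3: 21 sites. The prognostic strength of the baseline values for live birth is not in the document and is assumed below.

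**1. The plan's own figure.**
- Dropout: 200/(1 − 0.20) = 250 per arm, as stated.
- Four-arm trend test with scores 3, 2, 1, 0 (centred 1.5, 0.5, −0.5, −1.5). Signal: 200 × (0.375 + 0.075 − 0.075 − 0.075) = 60. Null SD: √(0.15 × 0.85 × 200 × 5) = 11.29. SD under Table 3: √118.5 = 10.89. Power = Φ[(60 − 2.432 × 11.29)/10.89] = Φ(2.99) = 99.9%.

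The bound of 80% therefore holds for the trend test.

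**2. The planned Pearson test on each hypothesis, unadjusted.** Power = Φ{[d − z√(2p̄(1−p̄)/n)] / √[(p₁(1−p₁) + p₀(1−p₀))/n]}, n = 200.
- A versus B: Φ[(0.10 − 2.432 × 0.0400)/0.0397] = Φ(0.068) = 52.7%.
- C versus D: Φ[(0.10 − 2.432 × 0.0300)/0.0296] = Φ(0.914) = 82.0%.
- B versus C: 15% in both arms, so there is no projected difference to detect.

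**3. What adjustment adds.** Simulation: logit of live birth = arm intercept + s × score, with a standard normal score, s from 0 to 1.05, and intercepts set to keep the Table 3 rates. There were 5,000 replicates at 200 per arm and level 0.015, comparing Pearson with the likelihood-ratio test of arm in the adjusted logistic model. Simulation error is about 0.7 points per figure.

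| Assumed c-statistic | A vs B, % | Gain | C vs D, % | Gain |
|---|---|---|---|---|
| 0.50 (no prognostic value) | 52.5 → 52.7 | 0.2 | 82.9 → 83.8 | 0.9 |
| 0.60 | 53.0 → 54.2 | 1.2 | 84.3 → 85.0 | 0.7 |
| 0.65 | 53.9 → 56.6 | 2.7 | 82.9 → 84.5 | 1.6 |
| 0.70 | 53.1 → 56.9 | 3.8 | 84.2 → 87.0 | 2.8 |
| 0.76 | 53.2 → 61.8 | 8.6 | 83.1 → 87.8 | 4.7 |

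A repeat with 6,000 replicates gave gains of 1.3, 2.4, 5.2 and 8.2 points for A versus B at c = 0.60 to 0.76, and 1.0, 1.7, 2.9 and 4.4 for C versus D. The first row shows that nearly a point of the C versus D gain comes from replacing Pearson by a likelihood-ratio test, not from the covariate. A simulation with two covariates gave 54% to 56–57% for A versus B and 84% to 85–86% for C versus D.

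In women: the formula in step 2 gives 55.2% at 210 per arm and 56.4% at 215 for A versus B. A gain of 2.5 to 3.7 points is thus worth about 10 to 15 women per arm. Reaching 80% needs 342 per arm.

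**4. Type I error.** For B versus C the adjusted test rejected in 1.4–1.5% of runs, against a nominal 1.5%. Two covariates without site terms gave about 1.2–1.7%. A pairwise fit with 21 site terms and five covariates gave about 1.9–2.3% at a 10% event rate and 2.0–2.5% at 5%.

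The reason is sparse sites. C versus D expects 200 × 0.15 + 200 × 0.05 = 40 live births for 27 parameters (intercept, arm, 20 site indicators, 5 covariates). With equal sites there are about 9.5 women per arm per site. The chance that a site has no event is (0.85 × 0.95)^9.5 ≈ 0.13, and the chance of at least one such site is 1 − 0.87^21 ≈ 95%. In a four-arm fit the per-site chance falls to (0.75 × 0.85 × 0.85 × 0.95)^9.5 ≈ 0.002.

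**The case against.** The strongest reply is that nothing here is an error. A Pearson chi-square is valid under randomisation, and the supportive covariate list is open, so a fuller list may stand in an analysis plan that is not shown. The secondary models that include BMI also contain treatment arm, so they already give a BMI-adjusted arm effect on a nearly identical outcome. All of this stands. The point is one of efficiency.

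The prognostic argument is also thinner than it looks. The Introduction speaks of ovulation on clomiphene. It mentions neither live birth nor age, and says nothing about women on placebo clomiphene, who make up all of C versus D. That stands too, and is why the c-statistic is shown as a range.

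A reader might infer more: that the primary analysis is biased, that the plan ignores BMI altogether, or that lack of adjustment explains the low power of A versus B. The documents support none of these. The first fails because of randomisation and the second because BMI is named in section 2.12. The third fails because the shortfall comes from attaching a trend-test figure to pairwise hypotheses.

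Finally, adjustment can do harm if overloaded. A long covariate list with fixed site terms in pairwise fits raises type I error, so the covariate set must be small.

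**Conclusion.** The point holds as a modest improvement, not as a fault of validity. Section 2.12 fixes an unadjusted primary test and names no patient-level factor except prior exposure in the supportive comparison of arms, although prognostic candidates are already collected.

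For an assumed c-statistic of 0.60 to 0.70, adjustment gains about 1 to 4 points for A versus B (5 in one of the two runs at 0.70) and 1 to 3 for C versus D, where part of the gain is due to the change of test. B versus C gains nothing. Gains of 8 to 9 points for A versus B need a c-statistic near 0.76, for which the document offers no support.

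Even then A versus B reaches only about 62%, so the stated power above 80% remains a separate matter. The figures rest on Table 3, 200 effective women per arm, the 0.015 level and a pairwise fit. The recommended four-arm model was not itself simulated.

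**What to change.** In section 2.12:

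- Prespecify age, BMI and prior clomiphene exposure as covariates for the live-birth contrasts, with log fasting insulin or log testosterone as an optional addition.
- Fit one logistic model to all four arms and report each contrast as a standardised risk difference with its confidence interval.
- Keep the Pearson chi-square as the unadjusted analysis, and state in advance which of the two carries the 0.015 level. The power gain arises only if it is the adjusted one.
- Do not enter 21 site indicators as fixed effects in pairwise fits. Handle site by a random effect, by pooling small sites or by a stratified method.

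If the primary test is to stay as it is, naming age and BMI in the supportive model would at least close the open list.

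The cost is a simple rule for missing baseline values, a decision on how site is handled, and slightly more analysis work. No new data are needed.

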### 2.3. Randomization

Randomization takes place as soon as the eligibility requirements are met. Participants are randomized into one of the four treatment arms: (1) true acupuncture and CC, (2) control acupuncture and CC, (3) true acupuncture and placebo CC, and (4) control acupuncture and placebo CC by an interactive online computer program in a central office. Using a 1 : 1 : 1 : 1 treatment ratio, there will be 250 women assigned to each treatment group and we expect the dropout rate would be 20%. The randomization is stratified within each of the participating sites by a random block algorithm. The data coordinating center (DCC) statisticians generated and validated the randomization scheme for the study before it was implemented in a web-based database system, and the study coordinator at each participating site logs on the web-based system to retrieve the randomization number after a patient is ready for it. The CC and placebo CC assignments are double-blinded, unknown to patients and study investigators except the DCC data manager. The true and control acupuncture treatments are known only to the TCM specialist (besides the DCC data manager) of the participating site that performs the randomized procedure. 

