### 2.9. End of Treatment Visit

At the end of study, a visit will be arranged for all women. The end of treatment visit should be performed as early as possible in pregnant women. A brief physical examination including acne and hirsutism assessment and a final assessment of adverse events and concomitant medications will be performed. Subjects will return the remaining study drug and their journal logs. All baseline measures will be repeated in all subjects. 

The blood samples done at the baseline visit and the end of the treatment visit will be shipped to the core laboratory for analysis. 

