Sign consent	×										
History	×										×
Urine pregnancy test	×		×	×	×	×	×	×	×	×	
Physical examination	×										×
Transvaginal ultrasound	×										×
Semen analysis	×										
Hysterosalpingogram	×										
Safety eligibility lads	×										×
Fasting phlebotomy for study parameters		×									×
Depression, anxiety, and quality of life questionnaires	×										×
Credibility check questionnaire			×		×						×
Progesterone assay	×			×		×		×		×	×
HCG assay	×			×		×		×		×	×
Acupuncture treatments (twice weekly)			×	×	×	×	×	×	×	×	
Assess adverse events and concomitant meds				×		×		×		×	×

Credibility check questionnaires are completed on the third acupuncture treatment and the last acupuncture treatment.

HCG: HCG concentrations will be measured once a week during the study period. If serum HCG concentration is elevated above 10 IU/L, pelvic ultrasound will be arranged 2 weeks later for the number of the gestational sacs and the viability of the pregnancy.

**Table 3 tab3:** The respective live birth rates in each intervention.

Interventions	True acupuncture	Control acupuncture
CC	*A* = 25%	*B* = 15%
Placebo CC	*C* = 15%	*D* = 5%

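### For hormones measured only at baseline and end of treatment, the stated mixed model amounts to comparing mean changes; using the baseline value as an adjustment would be more precise at no cost (secondary outcomes only)

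*Protocol article*

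**What the plan says.** Section 2.12 of the protocol article lists among the secondary outcomes "change in hormonal profile: FSH, LH, T, SHBG, and DHEAS". For outcomes of this kind, with hormone levels as the example, it states that "a linear mixed-effects model will be fit where the main independent variables will be treatment group, time, and their interaction", and adds "as well as the designed randomization stratification factors as covariates". Section 2.3 identifies the stratification factor as site: "The randomization is stratified within each of the participating sites by a random block algorithm". The baseline value is not named as a covariate, and no common baseline mean is stated.

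The visit schedule gives two occasions for these hormones:

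- Section 2.5: "All baseline measures will be repeated in all subjects at the end of visits".
- Section 2.9 sends to the core laboratory "The blood samples done at the baseline visit and the end of the treatment visit".
- Table 2, row "Fasting phlebotomy for study parameters", is marked at the baseline visit and the end of treatment visit only.

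The weekly assays in Table 2 are progesterone and hCG. Neither is in the hormonal profile outcome.

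**The concern.** A time effect and a treatment-by-time interaction cannot be estimated from a single post-treatment value. With two occasions, baseline must therefore be one of the responses. A treatment main effect in such a model lets the arms have different baseline means. Randomisation makes the true baseline means equal, so these are parameters known in advance to be the same, and estimating them separately costs precision.

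At stake is the width of the confidence intervals, and hence the power, for the hormone comparisons. The same would apply to "change in metabolic profile: glucose and insulin concentrations, cholesterol, triglycerides, HDL-C, and LDL-C" and to the quality-of-life, anxiety and depression change outcomes if they are analysed with the same model. Live birth, its sample size and its stated power are not involved.

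**Working it through.** **Inputs from the article.** Model terms and covariates (2.12); two occasions (2.5, 2.9, Table 2); 200 effective and 250 randomised women per arm with 20% dropout (2.11). The only stated figure that bears on this is the inflation, and it reproduces: 200 / (1 − 0.20) = 250. The article gives no figure for the mixed model itself.

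**Assumptions.** The article does not give the baseline-to-end correlation r (within arm and site) or the SDs s0 (baseline) and s1 (end of treatment). A range of r is shown. The first two steps of arithmetic take s0 = s1; the third relaxes this.

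**1. Complete pairs.** Per woman, the variance that drives each arm contrast is:

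- planned model (difference in mean change): s0² + s1² − 2·r·s0·s1, which is 2(1 − r)s² with equal SDs;
- baseline-adjusted: s1²(1 − r²), which is (1 − r²)s² with equal SDs.

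The ratio is 2(1 − r)/(1 − r²) = 2/(1 + r). The standard error ratio is its square root, and the equivalent share of the sample lost is 1 − (1 + r)/2 = (1 − r)/2.

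**2. A fraction f of end values observed, missing completely at random.** With N randomised per arm and fN completers, in units of s², the free-mean model has variance (1 − r²)/(fN) + (1 − r)²/N, against (1 − r²)/(fN) with adjustment. The ratio is 1 + f(1 − r)/(1 + r). At r = 0.5 and f = 0.8 this is 1 + 0.8 × 0.5/1.5 = 1.27.

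| r | Variance ratio, complete | SE excess | Sample equivalent | Variance ratio, 20% missing | SE excess |
|---|---|---|---|---|---|
| 0.3 | 1.54 | 24% | 35% | 1.43 | 20% |
| 0.5 | 1.33 | 15% | 25% | 1.27 | 13% |
| 0.7 | 1.18 | 8% | 15% | 1.14 | 7% |
| 0.8 | 1.11 | 5% | 10% | 1.09 | 4% |
| 0.9 | 1.05 | 3% | 5% | 1.04 | 2% |

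In power terms, take an effect that the adjusted analysis detects with 80% power, with 200 complete pairs per arm and an assumed alpha of 0.05. Under the planned model it has 62%, 68%, 73%, 76% and 78% power at these five values of r.

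**3. Unequal SDs.** Subtracting the two variances gives an excess of (s0 − r·s1)² for the planned model. This is never negative, so in large samples adjustment cannot lose precision, but the excess can vanish. With r = 0.5, s0 = 1 and s1 = 1.5, the planned variance is 1 + 2.25 − 1.5 = 1.75 and the adjusted variance is 2.25 × 0.75 = 1.6875. The ratio 1.6875/1.75 = 0.96 is a loss of about 4% of the sample. With s1 = 2 the loss is zero. An end SD below the baseline SD would make the loss larger than in the table.

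**4. Simulation check** (300 runs, two arms of 200, r = 0.5, equal SDs). With complete data the interaction estimate equalled the difference in mean change in every run (largest gap 6 × 10⁻¹⁵). In one example data set the standard errors were 0.0997 (planned), 0.0875 (baseline as covariate) and 0.0858 (common baseline mean). The simulated variance ratio of planned to covariate-adjusted was 1.28 (theory 1.33). With 20% of end values missing it was 1.20 (theory 1.27), and the planned estimate was then close to the completers' change-score estimate but not identical. All estimators averaged about 0.20, the true difference.

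**The case against.** The best defence is that treatment, time and their interaction form a standard and valid model, and that the outcomes are defined as changes, so model and outcome agree. The sentence comes from a condensed article, speaks of main independent variables, and leaves room for an analysis plan to add the baseline value or constrain the baseline means. The validity point stands in full. The second point stands only in part: the article names both the model terms and the covariates, and followed literally they give the less precise analysis. The comment therefore concerns a stated method and does not rest on missing detail.

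Three stronger readings are tempting, and the article does not support them.

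- A reader might infer that the plan commits four of the ten secondary outcomes to this model. It names hormone levels as an example. For other outcomes measured over time it promises only methods for correlated data. Extending the point to metabolic, quality-of-life and mood outcomes is reasonable, but it is an inference.
- A reader might infer that the planned estimate is biased. It is off target only conditionally on an observed chance imbalance at baseline. Over randomisation it is unbiased, and its standard error already allows for such imbalance. This is the precision point in another form.
- A reader might take a loss of a quarter or a third of the women as established. Those figures need equal SDs, complete pairs and r of 0.5 or less. The article gives none of these, it expects 20% dropout, and its end of treatment visit includes pregnant women, so equal SDs cannot be presumed.

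**Conclusion.** The point holds as a free improvement to secondary analyses. As written, the model for the hormone outcomes compares mean changes and makes no further use of the baseline value. Type I error is kept and the plan contains no contradiction here; the cost is precision alone. Under equal SDs the loss is material at r of about 0.5 or below and small at r of 0.8 or above. Dropout of 20% reduces it slightly. It shrinks towards zero as s0 approaches r·s1. The direction does not depend on these assumptions: in large samples the adjusted analysis is never the less precise one.

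**What to change.** In section 2.12, for the hormone outcomes, specify one of two analyses:

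- keep both occasions as responses, with time and treatment-by-time but no treatment main effect, so that the arms share a baseline mean. Allow separate variances at the two visits, so that the gain does not rely on equal SDs; or
- analyse the end-of-treatment value by arm and site, with the baseline value as covariate.

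The two are close but not identical (compare the example standard errors above), so one should be named before unblinding. If the metabolic, quality-of-life, anxiety and depression change outcomes are to be analysed with the same model, the text should say so and apply the same form to them. The cost is one line of wording, with no new data, visits or participants.
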